**7-9. Pre-treatment and concomitant therapy**

Confirm that no prior therapy (chemotherapy, radiotherapy, etc.) has been given for the subject's disease within 4 weeks prior to the start of the study. Immunotherapy (tumor vaccine, etc.) must not have been administered within 12 weeks prior to case enrollment. Confirm that there are no exclusion criteria.

Anticancer agents, immunosuppressive agents (excluding steroids), immunoenhancing agents, radiation therapy, and surgery for the primary disease (including metastasized tumors) are prohibited during the period of study drug administration. Corticosteroids may be administered locally or systemically as pretreatment for administration of the investigational drug or for symptomatic improvement of complications and adverse events.

Intravenous infusion of zoledronic acid or pamidronate and subcutaneous injection of denosumab for bone metastases are allowed if they have been administered once every 4 weeks if they were continued prior to participation in this study. However, they should not be administered on the same day as the investigational drug.

The following vaccines should be administered concomitantly.

1. Inactivated vaccines [may attenuate the effect of the vaccine (response to vaccination is unknown)].

2. Live or attenuated live vaccines [appropriate measures should be taken if symptoms based on the original disease of the live vaccine inoculated develop (response to vaccination is unknown, and secondary infection by live vaccine cannot be ruled out)]. Treatment for other complications and adverse events should be available. Unapproved drugs and alternative therapies (e.g., folk remedies) are prohibited, but the use of food-like supplements is not prohibited.

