**7-10. Post-treatment**

There are no restrictions on post-treatment after discontinuation of treatment.

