**9-4-4. Survival surveys and post-treatment**

Survival period of patients who did not receive maintenance dosing and those who received maintenance dosing but discontinued it will be investigated until the end of the clinical trial as described in "14-3. In case of death, the date of death and the reason shall be noted in the case report form”.

If post-treatment was given, the details of the treatment, its duration, efficacy, and duration of response shall be investigated.

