**10-1-2 Definition of harmful events and side effects (harmful events with a negative causal relationship)**

An adverse event is any unfavorable medical event that occurs in a subject receiving an investigational drug. In other words, any unwanted or unintended signs (including abnormal changes in laboratory values), symptoms, or illnesses that occur when the investigational drug is administered, regardless of whether or not there is a causal relationship with the investigational drug. In addition, adverse drug reactions (adverse events for which a causal relationship cannot be denied) are all adverse events other than those judged to have a "no relationship" causal relationship to the investigational drug.

Signs, symptoms, and abnormal changes in laboratory values associated with a disease (diagnostic name) shall be treated as adverse events with the diagnostic name. However, if an atypical or extremely severe sign or symptom occurs in the disease, the individual sign or symptom as well as the diagnosis should be treated as an adverse event.

The observation period for adverse events will be from the date of the first dose of study drug to 12 weeks after the last dose. However, for Grade 3 or higher non-hematologic toxicity, the observation period for adverse events shall be up to 24 weeks.

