**11-4. Analysis items and methods**

Detailed analysis methods are described in the "Statistical Analysis Plan" and "Pharmacokinetic Analysis Plan" to be prepared separately.

1) Safety

(1) Number of DLT cases

The number of DLTs and the incidence rate of DLTs per treatment group in Phase Ia are shown.

(2) Occurrence of adverse events and adverse reactions

Adverse events that occurred in Phase Ia and Phase Ib are summarized in the table. All adverse events and adverse drug reactions are summarized by the MedDRA basic terms and by major organ category, and the number and percentage of adverse events for each treatment group are shown.

(3) Gene analysis

Exploratory studies will be conducted as necessary.

2) Efficacy

(1) Efficacy in eliminating regulatory T cells

Summary statistics are calculated for each treatment group.

(2) Antigen-specific antibody immune response

To be investigated in an exploratory manner for each treatment group.

(3) Anti-tumor effect

The number of responders and the percentage of responders (response rate) will be calculated for each treatment group.

(4) Progression-free survival (PFS)

Progression-free survival is calculated using the Kaplan-Meier method.

(5) Overall survival (OS)

Overall survival is calculated using the Kaplan-Meier method.

(6) Immunostimulatory effect

To be examined on an exploratory basis as necessary.

(7) Gene analysis

To be explored as necessary.

In addition, the relationship between regulatory T-cell elimination effect and anti-tumor effect, antigen-specific antibody immune response, etc. will be explored.

3) Pharmacokinetics

(1) Plasma Mogamulizumab concentration

Plasma concentrations of Mogamulizumab will be listed and descriptive statistics for each dose will be shown; plasma concentration trends of Mogamulizumab will be plotted graphically as individual subject data and mean (+ standard deviation) versus blood collection time on a real and log scale.

(2) Mogamulizumab pharmacokinetic parameters

Calculate the pharmacokinetic parameters for each subject as indicated in "8-3-1 Definition of primary endpoints 1) Phase Ia Part (2) Pharmacokinetics" and calculate descriptive statistics for each dose.

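### Adverse events are counted for 12 or 24 weeks after the last dose, through any next anticancer treatment, and the dose-group tables do not separate events that begin after that treatment starts

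*Protocol*

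**What the plan says.** Protocol section 10-1-2 defines an adverse event as any unfavourable event "regardless of whether or not there is a causal relationship with the investigational drug". It sets the window by time alone: the "observation period for adverse events will be from the date of the first dose of study drug to 12 weeks after the last dose", and "for Grade 3 or higher non-hematologic toxicity, the observation period for adverse events shall be up to 24 weeks". Footnote *10 to the schedule in 9-1 repeats both limits. Section 7-2 places the final safety evaluation at up to 24 weeks after the last dose.

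The ban on other anticancer treatment covers only the dosing period. Section 7-9 ends its list with "surgery for the primary disease (including metastasized tumors) are prohibited during the period of study drug administration", and section 7-10 adds: "There are no restrictions on post-treatment after discontinuation of treatment". Starting another treatment is not among the reasons for ending evaluation in 14-1-2.

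For the analysis, section 11-4 1)(2) states that "All adverse events and adverse drug reactions are summarized by the MedDRA basic terms" and by organ class, with numbers and percentages per treatment group. No cut or second table at the start of the next treatment is mentioned. On later treatment, section 9-4-4 says: "If post-treatment was given, the details of the treatment, its duration, efficacy, and duration of response shall be investigated".

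Type, frequency and severity of adverse events is a primary endpoint in both parts (8-1-1, 8-1-2). Phase Ib safety and regulatory T-cell elimination together inform the recommended dose (8-3-2).

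**The concern.** A patient who stops mogamulizumab may begin chemotherapy, radiotherapy or another trial drug while adverse events are still being counted. As 11-4 is written, events from that treatment are tabulated under the mogamulizumab dose group.

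The route is concrete. Section 9-5-4 requires a general blood test 12 weeks after the last dose, and section 10-1-1 turns any abnormal change from baseline into an adverse event. A fall in blood counts caused by chemotherapy at that visit is therefore recorded. Low blood counts and raised AST/ALT are also common mogamulizumab reactions (section 1-4: neutropenia 55.8%, ALT increase 39.5%), so the two sources are hard to tell apart afterwards.

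At stake is how to read the all-cause frequencies: how toxic each dose looks, and whether one dose looks worse than the other when the Phase II dose is chosen.

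**Working it through.** The protocol gives no figure to reproduce for this point, and Phase Ib has 20 patients per group on grounds of studying T-cell removal and feasibility (7-6-2). The check is window arithmetic followed by an illustration.

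**1. Window length.** Put dose 1 on day 0. Eight weekly doses (7-7) put dose 8 on day 49. The standard window ends on day 49 + 84 = 133, and the long window on day 49 + 168 = 217. The part after the last dose, when any treatment is allowed, is 84/133 = 63% (12 of 19 weeks) and 168/217 = 77% (24 of 31 weeks). These two shares need no assumption about later treatment. They apply to a patient without maintenance dosing; maintenance lengthens time on drug and lowers them.

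**2. Share under the next treatment.** Share = (window end − start day) / window end. The start days are assumptions.

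| Case | Standard window | Long window |
|---|---|---|
| 8 doses, start on day 112 | (133 − 112)/133 = 21/133 = 16% | (217 − 112)/217 = 105/217 = 48% |
| 8 doses, start on day 84 | (133 − 84)/133 = 49/133 = 37% | (217 − 84)/217 = 133/217 = 61% |
| 4 doses (last on day 21), start on day 35 | (105 − 35)/105 = 70/105 = 67% | (189 − 35)/189 = 154/189 = 81% |

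For four doses the windows end on day 21 + 84 = 105 and day 21 + 168 = 189. These are shares of days for a patient who does start new treatment. They are not event rates.

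**3. What this could do to a frequency.** Let p be the true study-drug rate of some event, s the share of patients who start new treatment in the window, and q the event rate on that treatment. Assuming independence, the tabulated rate is 1 − (1 − p)(1 − s·q). All three inputs are assumptions.

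- Within a group, p = 20% and s = 60%:
  - q = 20% gives 1 − 0.80 × 0.88 = 29.6%.
  - q = 40% gives 1 − 0.80 × 0.76 = 39.2%.
  - In 20 patients this is 1.9 to 3.8 extra patients with the event.
- Between groups, the same p = 20% in both, s = 30% against 70%:
  - q = 20% gives 24.8% against 31.2%, a spurious gap of 6.4 points.
  - q = 40% gives 29.6% against 42.4%, a spurious gap of 12.8 points.
  - If s is equal in both groups, the gap is zero.

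**The case against.** **It belongs in the analysis plan.** Section 11-4 leaves detailed methods to a separate statistical analysis plan, which is not available here and may already contain the split. That is possible. But the protocol itself fixes the window, the all-cause definition and the all-event table per group, and someone following it as written would produce the mixed table.

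**Causality assessment already handles it.** Each event is judged for its relation to study drug, with time course and other causes considered (10-2-8), and adverse reactions are tabulated as well. This stands in part, but the filter does not touch the all-event table. It also removes only events judged to have no association; every other event counts as an adverse reaction (10-1-2). The persistence of low CCR4-positive T cells described in 1-3-1-2 might seem to make that judgement harder, but it comes from macaques and was seen without signs of toxicity, so it carries little weight.

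**A cut has its own bias.** Patients who start new treatment early would have shorter follow-up in a truncated table. Section 10-5-2 notes severe skin disorders several weeks after treatment ends, so genuine delayed toxicity could drop out. This stands, and it is why the full-window table should stay beside the split.

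**Uptake may be low.** Many eligible patients have no suitable standard treatment left, or have refused it (4-1). This is fair, and it is one reason why the size cannot be stated.

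A reader might infer that the whole primary safety endpoint is compromised. It is not: dose-limiting toxicity, and the maximum tolerated dose with it, rests on the first 28 days and on events whose link to study drug cannot be ruled out (8-3-1).

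**Conclusion.** The point holds for the all-cause adverse-event frequencies per dose group. These are part of the primary safety endpoint and feed a descriptive review, with no formal test between doses. As written, the tables can include toxicity of the next treatment, which inflates the frequencies in each group where patients start one. The protocol should be changed.

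The size cannot be derived from the documents. The day shares of 16% to 67% (standard window) and 48% to 81% (long window) rest on assumed start days and apply only to patients who start treatment within the window. The extra patients and the spurious gaps rest on assumed rates throughout.

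It is tempting to add that the dose whose patients progress sooner will collect more of the next treatment's toxicity. Such an imbalance is possible but not shown: nothing in the protocol indicates a difference in progression between doses, and Phase Ib with two groups is randomised with minimisation by carcinoma (7-5-2).

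**What to change.** Leave the collection window, serious-event reporting and the full-window table as they are. No rule on later treatment needs to change. Two additions to the protocol:

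- **Section 11-4 1)(2):** also present adverse events and adverse reactions per dose group, split by onset before versus on or after the start of the next anticancer treatment. Name the pre-start table as the main basis for comparing doses, with later events judged drug-related shown beside it. Give the length of follow-up before the next treatment per group.
- **Section 9-4-4:** state that the start date of post-treatment is recorded. The section asks for details and duration but does not name the date, and recording of concomitant therapy ends 4 weeks after the last dose (9-3), well before the adverse-event window closes.

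Event onset dates are already collected (10-2-2), so the cost is one extra table and one date field. The remaining drawback is unequal follow-up in the pre-start table, which is why its length should be shown. If the statistical analysis plan already contains the split, 11-4 need only refer to it, and the start date is the only item left to add.

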**10-1-3. Definition of harmful signs of rehabilitation**

Serious adverse event" means any of the following

1) Death

2) An event that may lead to death

3) An event requiring hospitalization or prolonged hospitalization for treatment

4) Disability

5) An event that may lead to disability

6) Events as serious as those listed in 1) to 5)

7) Congenital disease or abnormality in later generations

The following events are not regarded as serious adverse events.

When "hospitalization or prolonged hospitalization" occurs due to the administration of the investigational drug.

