**1-4. Side effects**

The incidence of adverse reactions (including laboratory test abnormalities) in 43 safety evaluation subjects in the domestic clinical study was 100% (43/43 subjects). The most common adverse reactions (≥10.0%) were lymphopenia in 41 patients (95.3%), infusion reaction in 37 patients (86.0%), fever in 34 patients (79.1%), leukopenia in 29 patients (67.4%), neutropenia in 24 patients (55.8%), chills in 24 patients (55.8%), thrombocytopenia in 23 patients (53.5%), rash in 18 patients (41.9%), ALT (GPT) increased in 17 patients (39.5%), AST (GOT) increased in 16 patients (37.2%), LDH increased in 13 patients (30.2%), tachycardia in 12 patients (27.9%), ALP increased in 11 patients (25.6%), hypoxemia in 9 patients (20.9%), hemoglobin decreased in 9 patients (20.9%), and, nausea in 8 patients (18.6%), increased blood pressure in 8 patients (18.6%), hypoalbuminemia in 7 patients (16.3%), pruritus in 6 patients (14.0%), weight gain in 6 patients (14.0%), decreased albumin in 5 patients (11.6%), increased γ-GTP in 5 patients (11.6%), headache in 5 patients (11.6%), and hypertension in 5 patients (11.6%)., etc. Serious adverse reactions reported at the time of application included infusion reaction (86.0%), severe skin disorder, infection (4.7%), fulminant hepatitis caused by hepatitis B virus (frequency unknown), hepatitis (2.3%), tumor disruption syndrome (2.3%), severe hematologic toxicity, and hepatic dysfunction.

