**4-1. Selection criteria for patients**

Patients with advanced or recurrent solid tumors who meet all of the following criteria at the time of enrollment will be eligible.

1) Patients whose tumor cells are negative for CCR4 expression (diagnosis should be made using a method commercialized in Japan) and whose histopathological diagnosis of malignancy such as lung cancer, gastric cancer, esophageal cancer, malignant melanoma, or ovarian cancer is confirmed.

2) Patients who are refractory or intolerant to standard treatment, have no appropriate treatment, or have refused standard treatment.

3) Patients with a performance status (ECOG criteria) of 0, 1, or 2

4) Patients must be at least 20 years of age on the date of obtaining consent to participate in the clinical trial.

5) No severe damage to major organs (bone marrow, heart, lungs, liver, kidney, etc.) and laboratory values (within 2 weeks prior to enrollment) that meet the following criteria

Neutrophil count: 1,500/μL or more

Hemoglobin level: 8.0 g/dL or higher

Platelet count: 75,000/μL or higher

Serum total bilirubin level: 2.0 mg/dL or less

AST (GOT), ALT (GPT): not more than 2.5 times the upper limit of the facility standard (not more than 5.0 times the upper limit of the facility standard if the cause is judged to be hepatic infiltration due to the primary disease)

Serum creatinine: 1.5 mg/dL or less

Arterial blood oxygen saturation: 93% or higher (room temperature)

Electrocardiogram: No abnormal findings requiring treatment

Left heart ejection fraction (by echocardiography): 50% or more

6) The patient must agree to use a condom or other contraceptive method from the time of consent until 24 weeks after completion of study drug administration (excluding postmenopausal women (more than 1 year after the last menstrual period) or women who have undergone surgical sterilization and men who have undergone surgical sterilization)

7) The patient has given written consent.

8) Patients who are able to be hospitalized for the administration of Mogamulizumab from before the first dose until the day after the first dose.

9) Patients with measurable lesions in RECIST ver. 1.1 (New response evaluation criteria in solid tumours:Revised RECIST guideline (version 1.1)^12)^. Patients must have measurable disease at

10) Expected survival of at least 3 months.

<Rationale for setting>

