**9. Observation items and methods**

**9-1. Clinical trial schedule**

The prescribed observations and examinations will be conducted according to the following schedule1. Patients will be hospitalized from before the first administration to the day after the first administration.

For subjects in Phase Ia, the investigators will obtain consent for the continuation of the clinical trial again prior to the 5th administration.

After 8 doses, if the subject has shown a regulatory T-cell elimination effect and antigen-specific antibody immunoreactivity or SD or higher on RECIST, the investigator may continue to administer the investigational drug if the subject wishes to receive maintenance dosing and the investigator determines that maintenance dosing is appropriate.

The first dose of investigational drug is defined as 1 week.

[figure not shown]
Table 1. Clinical trial schedule

○：Additional items to be performed when maintenance dosing is performed after 8 doses.

*1: The ninth and subsequent doses of the investigational drug should be administered only when SD or better is confirmed in the regulatory T-cell elimination effect and antigen-specific antibody immunoreactivity or RECIST, the subject wishes to receive a maintenance dose of the investigational drug, and the investigator and others consider that the maintenance dose of the investigational drug is appropriate.

*2: Continuous observation from before the start to the end of study drug administration.

*3: To be conducted before administration of the investigational medicinal product during the period of administration of the investigational medicinal product.

*4: Before administration of the investigational drug, at 30 minutes, 1 hour, 1.5 hours after the start of administration, at the end of administration, 30 minutes and 1 hour after the end of administration.

*5: If it is difficult to collect the prescribed volume of blood due to signs of anemia, etc., the following tests should be performed in consideration of subject safety: 1. General blood test (facility prescribed volume), 2. Thyroid function test (facility prescribed volume), 3. Regulatory T cell test (10 mL), 4. Pharmacokinetic test (Phase Ia part only, 2 mL), 5. Antigen-specific antibody immunological reaction test (5mL), 6. Genetic analysis (15mL), 7. Immunopotentiation effect test (30~50mL), 8. Tumor markers (facility's specified volume), as much blood as possible in the order of priority.

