**10-3. Adverse event reporting and response**

Adverse events that must be reported are those that occur during the observation period of adverse events defined in "10-1-2. Definition of adverse events and adverse reactions (adverse events for which a causal relationship cannot be ruled out)" and "Serious adverse events" defined in "10-1-3. When such an adverse event occurs”, it should be reported in accordance with "10-3-1. Serious Adverse Event Reporting Procedures”.

In addition, if an adverse event that is not a serious adverse event but meets the criteria for DLT (defined in 8-3-1. Primary Endpoints) occurs in the Phase Ia portion, regardless of whether or not there is a causal relationship, the investigator should take appropriate measures, prepare a "Report on Adverse Events Related to Dose Increases" and promptly submit it to the Trial The report shall be promptly submitted to the Clinical Trial Coordinating Committee.

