**10-3-1. Serious adverse event reporting procedures**

1) Immediate report (within 24 hours from the time of knowledge of the occurrence)

In the event of a reportable adverse event, the investigator shall take appropriate measures and report it to the head of the site, regardless of whether there is a causal relationship with the investigational drug or not, and shall immediately (within 24 hours from the time when he/she becomes aware of the occurrence) submit a "Report on Serious Adverse Events (Medical Form 12-1)" to the site's coordinating committee, stating the information available at that time. The information available up to that point shall be reported to the Clinical Trial Coordinating Committee.

2) Detailed report (within 3 days from the time when the investigator becomes aware of the occurrence)

The investigator shall prepare the "(Medical) Form 12-1, 2 Report on Serious Adverse Events" within 3 days of learning of the occurrence of a serious adverse event, and report it to the head of the investigational site as well as to the Clinical Trial Coordinating Committee. At that time, the relationship between the investigational drug and the adverse event should be fully considered. However, if the adverse event is a fatal or life-threatening serious adverse event for which a causal relationship with the unknown investigational drug cannot be denied, a detailed report shall be submitted to the TIC immediately (the next day at the latest). The TIC shall also immediately notify the investigators and investigational drug providers at other sites.

3) Response

The investigator who conducts the clinical trial himself/herself shall consider how to respond and take necessary measures under the coordination of the Clinical Trial Coordinating Committee. In case of administration of the investigational drug or discontinuation of the clinical trial, the investigator must promptly report to the Clinical Trial Coordinating Committee.

The TIC shall also request the Efficacy and Safety Evaluation Committee to deliberate and decide whether the clinical trial should be continued or not.

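### The hospitalisation exemption in the serious adverse event definition (10-1-3) is not limited to the planned dosing stay, so as worded it also covers stays caused by a drug reaction

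*Protocol*

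**What the plan says.** Section 10-1-3 of the protocol lists seven criteria for a serious adverse event. The third is "An event requiring hospitalization or prolonged hospitalization for treatment". After the list comes an exemption, introduced by "The following events are not regarded as serious adverse events". It has one entry: hospitalisation or prolonged hospitalisation that "occurs due to the administration of the investigational drug". No planned stay, dose number or absence of an adverse event is mentioned.

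The protocol schedules one hospital stay. Inclusion criterion 8 in section 4-1 asks for "Patients who are able to be hospitalized for the administration of Mogamulizumab from before the first dose until the day after the first dose", and section 9-1 states that "Patients will be hospitalized from before the first administration to the day after the first administration". The rationale for criterion 8 is subject safety if an injection-related reaction occurs.

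Section 10-3-1 requires serious events to be reported within 24 hours, "regardless of whether there is a causal relationship with the investigational drug or not". The coordinating committee must also refer the matter to the Efficacy and Safety Evaluation Committee, which reviews the serious adverse event report under 10-3-2. Section 10-3 adds a separate report for Phase Ia, to be made "if an adverse event that is not a serious adverse event but meets the criteria for DLT".

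**The concern.** The exemption reuses the vocabulary of criterion 3 and makes a link to drug administration the reason for removing an event from the definition. Taken at its word, a patient kept in hospital because of an infusion reaction, or readmitted with a drug-related rash, does not have a serious event on the ground of hospitalisation. A patient admitted for an unrelated reason does.

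What is at stake is the expedited safety pathway. The 24-hour report, the detailed report, the referral to the Efficacy and Safety Evaluation Committee and the serious/non-serious code in 10-2-4 all depend on this definition. Sites apply the text as it stands, and two sites could reasonably code the same event differently.

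**Working it through.** The protocol has no figure of its own to reproduce here. The check compares the provisions, followed by one piece of arithmetic on scale.

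**1. Criterion 3 against the exemption (both in 10-1-3).** Criterion 3 covers an event that requires or prolongs hospitalisation for treatment. The exemption covers hospitalisation or prolongation arising from drug administration. A stay extended to treat an infusion reaction meets criterion 3 and, read literally, also meets the exemption. The section does not say which prevails.

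**2. The exemption against the planned stay (4-1, 9-1).** The scheduled stay begins before dose 1 and ends the day after it. Exempting that stay is sensible, since without an adverse event it is not an event at all. However, the exemption also names prolonged hospitalisation. The scheduled stay has a fixed end and exists because injection reactions are expected, so a reaction is the most natural reason for extending it.

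**3. The exemption against the reporting rules (10-3, 10-3-1, 10-1-4).** Reporting is meant to be independent of causality, yet the exemption turns on a link to the drug. Section 10-1-4 sends worsening of the underlying disease through serious event reporting if it meets 10-1-3. On the literal reading, admission for progression is therefore reported within 24 hours and admission for a drug reaction need not be. Sections 10-3 and 10-3-1 take their definition from 10-1-3, so they cannot restore what the exemption removes.

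**4. What else would catch these events.**
- The other criteria in 10-1-3 (death, possible death, disability, possible disability, equal seriousness, congenital abnormality) do not depend on hospitalisation. An event meeting one of them stays serious. Only events serious through criterion 3 alone are exposed.
- The extra report in 10-3 applies only in Phase Ia and only to events that meet the DLT criteria. Under 8-3-1, injection-related reactions count as DLTs from Grade 4, apart from the dose-delay provisions. A Grade 3 reaction that prolongs the stay could therefore miss both routes.
- Phase Ib has 20 or 40 patients (7-6-2), against 9 to 18 in Phase Ia (7-6-1), and has no comparable fallback.
- Every adverse event is still entered in the case report form (10-1-4), graded by CTCAE v4.0 (10-2-3) and tabulated by treatment group (11-4).

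**5. Scale.** The protocol does not say how often a drug reaction led to admission or a longer stay. Two figures are nearby.
- Any infusion reaction: section 1-4 reports "infusion reaction in 37 patients (86.0"%), that is 37/43.
- Grade 3 or higher injection reaction: 1 of 43 (section 10-4, item 2). 1/43 = 2.3%, and 40 × 1/43 = 0.93, so about 1 in 40 patients. With one Phase Ib group of 20, 20 × 1/43 = 0.47.

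The second figure is the closer of the two, but grade is not the same as length of stay. It comes from ATL and PTCL patients, and it says nothing about admissions for other drug effects. It indicates order of magnitude only.

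**The case against.** The strongest reply is that the sentence means hospitalisation for the purpose of giving the drug. Criterion 3 speaks of hospitalisation for treatment, the exemption speaks of the act of administration, and 4-1 uses the same idea for the planned stay. Prolongation could then refer to an inpatient kept longer for dosing. The English text also shows translation faults: the heading of 10-1-3 refers to rehabilitation although the section defines serious events. On this view an admission to treat a reaction falls under criterion 3 and nothing is lost.

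Most of this stands. The benign reading is probably what was intended, and a reader should not infer a plan to keep drug-caused admissions out of the reports. It does not settle the matter, because no provision states the limit and the exemption comes after the criteria it qualifies. Criterion 6, on events of equal seriousness, leaves room to report, but as a judgement by the site.

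Two stronger inferences are tempting and are not supported:

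- **That the primary safety endpoint is biased.** Sections 8-1-1 and 8-1-2 define it by type, frequency and severity, with severity graded by CTCAE. None of these uses the serious/non-serious code, and 11-4 names no serious-event rate by dose.
- **That several unreported events can be predicted.** One could take 86% of 40 patients, about 34, and apply a guessed share of prolonged stays. No such share is given. The 86% is also the proportion of patients reacting over repeated doses, whereas the mandatory stay covers dose 1 only.

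**Conclusion.** The point holds as a defect of wording in an operative safety rule. The exemption in 10-1-3 is broader than the planned dosing stay it probably has in mind, and it conflicts with criterion 3 and with the causality-independent reporting in 10-3-1. The consequence is confined to events that are serious only through hospitalisation. They could be coded non-serious and so miss the 24-hour report and committee review, with a fallback only for DLT-type events in Phase Ia. Recording and grading of these events as adverse events are unaffected.

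The number of events cannot be estimated from the protocol. The Grade 3 or higher injection reaction rate, about 1 in 40, is the nearest guide, on the assumptions that grade stands in for prolonged stay and that the earlier ATL and PTCL patients resemble this population. The conclusion does not rest on that number. The correction is worth making because the rule governs expedited safety reporting and costs almost nothing to repair.

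**What to change.** Reword the exemption in 10-1-3 so that it covers only protocol-scheduled hospitalisation for giving the drug or for planned observation, without an adverse event. Add that any admission, or any prolongation of a stay, because of an adverse event remains serious under criterion 3, including when the event is a reaction to the drug. Sections 10-3 and 10-3-1 then work as written and need no change.

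The cost is one sentence in the protocol, a notice to sites and possibly a few more serious adverse event reports. No dose, schedule or treatment rule is affected.
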